#### Other measures

Development and Well-being Assessment (DAWBA^29^): The DAWBA is a semistructured, investigator-based diagnostic interview for child mental health problems, including ADHD, which includes the (Strengths and Difficulties Questionnaire; SDQ^30^) as an initial screen. The parent and teacher DAWBA will be completed to compare the accuracy of clinic diagnosis (in QbO and QbB arms of the trial) to that of an independent clinical consensus diagnosis made using the DAWBA. Two experienced clinicians, blind to allocation, will review the DAWBA and arrive at a clinical consensus diagnosis.QbTest scores: Q-scores for attention, impulsivity and activity will be compared with DAWBA ADHD diagnosis to obtain the best predictive model based on QbTest scores that discriminates between ADHD ‘positive’ and ADHD ‘negative’ gold standard DAWBA diagnosis.Side-effects scale:^31^ Side-effects scale will be completed as a control check in medicated participants to ensure greater speed to diagnosis/medication normalisation is not off-set by greater side effects.SNAP-IV:^32^ The proportion of patients achieving symptom normalisation assessed via the SNAP-IV. If the young person receives a QbTest on medication (Qb2), the timing on the 3-month SNAP-IV will be moved to coincide with Qb2 to provide a direct comparison of subjective (SNAP-IV) and objective (QbTest) measures. The SNAP-IV is a rating scale designed to assess ADHD symptoms.SDQ:^30^ The SDQ is a brief behavioural screening questionnaire which can be used as part of a clinical assessment.C-GAS (Children's Global Assessment Scale^33^): Clinician opinion of patient outcome will be assessed via the C-GAS. The C-GAS is a 0–100 scale which that integrates psychological, social and academic functioning in children.EQ-5D-Y (EuroQol Five Dimensions Heath Questionnaire-Youth^34^): Child health-related quality of life will be assessed using the EQ-5D-Y.A resource collection profile tool will be used. It will encompass elements of a CSRI (Client Service Receipt Inventory^35^) often used in mental health studies but will be a specifically designed economic collection pro-forma for the purpose of this study. It will collect demographic details as well as information on all the services used by the child and family borne costs to be estimated. Indirect costs such as time lost from work incurred by the child's parents or carers will further be recorded. This measure will enable a societal wide perspective for a cost-effectiveness analysis of the QbTest. The DAWBA^29^ QbTest^22^ SDQ^30^ Side-effects scale,^31^ SNAP-IV^32^ C-GAS^33^ EQ-5D-Y^34^ and CSRI^35^ all have established reliability, validity and history of use in clinical and research settings.

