### Sample size and justification

The sample size calculation was based on an audit study data from the Department of Community Pediatrics at the Medway NHS Trust ([name], 2013, unpublished data). Calculations based on this audit study data showed that the mean number of visits needed to achieve an ADHD diagnosis before introduction of the QbTest (control rate) for children aged 6–14 year olds was 2.94 visits and following the introduction of QbTest a diagnosis was reached in a mean of 2.18 visits. Following consultation with stakeholders, it was agreed that this difference (2.94–2.18) represented the minimum clinically important difference, with any smaller difference in mean clinic visits being of debatable value. Therefore, 71 patients in each study group will be required to detect a mean count difference of the above magnitude with 80% power at two tailed 0.05 significance level^36^
^37^ assuming the number of visits follows a Poisson distribution.

Given the evidence that the intraclass correlation coefficients of mental health measures across General Practitioner (GP) centres is extremely low,^38–40^ and results from the Medway audit data indicate that the number of visits needed to achieve an ADHD diagnosis was homogeneous across centres, we will assume that centre effects will not influence the sample size calculation for this study. After taking into account a 20% attrition rate, the final total sample size will be 178. The same calculation performed with 90% power would require a total sample of 234 participants. We aim to recruit 178 participants as a minimum and 234 participants as a maximum. Software Stata V.13 was used for power analysis.

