### Data analysis plan

The analysis will be conducted on an intention-to-treat (ITT) basis. Exploratory analysis will be conducted first for outcome and patient background variables; descriptive statistics of each variable will be presented separately for each group at each follow-up point, with means and SD for normally distributed variables, medians (IQR) for skewed variables and frequency (percentage) for categorical variables. Missing values will be checked and reported. Multiple imputation will be used to hand missing values, based on a multilevel modelling approach.

To compare the number of visits needed to achieve an ADHD diagnosis (either confirmed or excluded) between groups, Poisson regression with binary group status as the explanatory variable will be implemented. To compare clinician's confidence in their diagnostic decisions, multilevel modelling with patient as a level 2 unit will be used to take into account the non-independence within patient data due to repeated measures.^41^

κ Statistics will be used to reflect the stability of diagnosis between first confirmed diagnosis and diagnosis rerated at 6-month follow-up time. κ Statistics will be reported for each group and the stability of diagnosis will be compared between arms using logistic regression. The same analysis approach will be implemented to explore the stability of diagnosis confidence between time of first confirmed diagnosis and 6-month follow-up. To assess the diagnosis accuracy, the sensitivity, specificity, likelihood ratio (LR) ve+, LR ve−, positive predictive value (PPV) and negative predictive value (NPV) will be reported for each group and the test performance will be compared between QbO and QbB arms.^42^
^43^ Receiver operating characteristic curve analyses will be used to obtain the best predictive model based on QbTest scores that discriminates between ADHD ‘positive’ and ADHD ‘negative’ gold standard DAWBA diagnoses.

For treatment related outcomes (phase 2) outcome measures such as SNAP-IV, side effects scale, SDQ and C-GAS scores, multilevel modelling with patient as a level 2 unit will be again applied to quantify the difference between QbO and QbB arms.

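### The exploratory QbTest ROC model is selected for discrimination in the trial's own sample with no correction described, so its performance would look too good if reported from the same children

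*Protocol article*

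**What the plan says.** Two places in the protocol article describe this analysis. Under Other measures: "Q-scores for attention, impulsivity and activity will be compared with DAWBA ADHD diagnosis to obtain the best predictive model based on QbTest scores". Under Data analysis plan: "Receiver operating characteristic curve analyses will be used to obtain the best predictive model based on QbTest scores". In both, the target is separation of DAWBA-positive from DAWBA-negative children.

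The article names no cut-off and no rule for choosing one. It does not say which performance measures will be given for the model, and it mentions no split sample, cross-validation, bootstrap or external data set.

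A different accuracy analysis stands just before it in the Data analysis plan: sensitivity, specificity, likelihood ratios and predictive values, given for each arm and compared between arms. Other measures explains what that analysis judges. The DAWBA is collected "to compare the accuracy of clinic diagnosis (in QbO and QbB arms of the trial) to that of an independent clinical consensus diagnosis". That is the clinicians' diagnosis, not the QbTest model.

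**The concern.** The model is to be the one that discriminates best, and discrimination is also how an ROC model is usually described. When weights, choice of scores or a cut-off are tuned to a sample and then graded on it, part of the apparent performance is chance fit to those children. The bias runs in one direction.

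At stake is how far QbTest scores alone appear to separate referred children. The Abstract says the findings are meant to inform commissioners, clinicians and managers. An uncorrected figure would sit beside the supplier's 85% sensitivity and 92% specificity, quoted in the QbTest section of the introduction, and could be read as a like-for-like result from routine clinics.

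**Working it through.** **Sample size available.** The article states that "71 patients in each study group will be required to detect a mean count difference of the above magnitude with 80% power", with Poisson means 2.94 and 2.18. The log rate-ratio formula is n = (1.960 + 0.842)² × (1/2.94 + 1/2.18) / [ln(2.94/2.18)]². This gives 7.849 × 0.7989 / 0.08945 = 70.1, so 71 per group. With 20% attrition, 2 × 71 / 0.8 = 177.5, so 178. At 90% power the formula gives 93.8, so 94 per group and 2 × 94 / 0.8 = 235, against 234 stated. The plan's figures reproduce within rounding.

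The article gives no N for the ROC analysis. Three values were used: 142 (2 × 71, the number left from 178 after 20% attrition), 178 (the stated minimum recruited) and 234 (the stated maximum). If 20% were lost from 234, 0.8 × 234 = 187 would remain, which lies between the last two.

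**Assumptions not in the article.** Normally distributed scores; three Q-scores (attention, impulsivity, activity) with pairwise correlation 0.4 and equal shifts; logistic weights; cut-off at the maximum Youden index; true AUC of the best combination 0.65, 0.75, 0.85 or 0.95; DAWBA ADHD prevalence 50% or 70%.

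**Formulas.** Let Σ be the score covariance matrix and d the mean shift in ADHD cases, scaled so that √(d′Σ⁻¹d) = √2 Φ⁻¹(AUC). Each simulated sample gives weights w and cut-off c. The true performance of that same rule is:
- sensitivity = 1 − Φ((c − w′d)/√(w′Σw))
- specificity = Φ(c/√(w′Σw))
- AUC = Φ(w′d/√(2w′Σw))

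The excess is the apparent value in the sample minus the true value, averaged over samples (600 per cell).

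**Excess in sensitivity plus specificity, percentage points in sum, three-score model:**

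| N | Prevalence | AUC 0.65 | AUC 0.75 | AUC 0.85 | AUC 0.95 |
|---|---|---|---|---|---|
| 142 | 50% | 11.9 | 9.2 | 8.0 | 5.7 |
| 142 | 70% | 13.3 | 10.9 | 9.0 | 6.2 |
| 178 | 50% | 10.2 | 8.0 | 6.9 | 4.5 |
| 178 | 70% | 11.8 | 9.1 | 7.8 | 5.8 |
| 234 | 50% | 8.6 | 6.9 | 5.8 | 4.1 |
| 234 | 70% | 9.4 | 7.8 | 6.2 | 4.7 |

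The excess is shared between the two measures, and falls more on specificity when ADHD cases are the majority. At N = 142 and AUC 0.75 it is 4.7 (sensitivity) and 4.4 (specificity) at 50% prevalence, and 3.7 and 7.1 at 70%.

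**Variants over the same grid:**
- One score with a chosen cut-off: 3.9 to 8.9 points at N = 142 to 178; 3.4 to 6.7 at N = 234.
- Best of the seven possible score subsets, plus cut-off: 5.6 to 15.9 points at N = 142 to 178; 4.9 to 12.3 at N = 234.
- AUC itself, for the multi-score models: about 0.2 to 3.9 points.
- Linear discriminant weights in place of logistic ones, AUC 0.70 to 0.95: about 5 to 14 points at N = 142 to 178 and 3.5 to 9 at N = 234, with 0 to 4 points in AUC.

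**Anchor in the article.** The supplier's 85% and 92% correspond to a Youden index of 0.85 + 0.92 − 1 = 0.77. Under an equal-variance binormal model, AUC = Φ((1.036 + 1.405)/√2) = Φ(1.726), about 0.96. Near that value (the AUC 0.95 column) the three-score excess is 4.5 to 6.2 points at N = 142 to 178 and 4.1 to 4.7 at N = 234. With a subset search it is 5.6 to 7.9 and 4.9 to 5.8.

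**The case against.** The strongest objection is that the point rests partly on silence. The article does not say that performance will be reported from the derivation sample. Internal validation is a detail that a condensed article may leave to a full protocol or SAP, and neither is shown. This stands as a limit: the conclusion must be conditional, and if a fuller document already specifies the correction, a cross-reference is enough. It does not remove the point, because choosing a model for its discrimination in the one sample described is a stated choice, and the direction of its bias is known.

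Three stronger readings are tempting, and the documents do not support them.

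- A reader might infer that the sensitivity and specificity promised for each arm are inflated. They concern clinic diagnosis against DAWBA consensus and involve no fitted weights or cut-off, so this optimism does not reach them.
- A reader might infer that the QbTest sensitivity and specificity will be about 10 points too high in sum. No cut-off is planned in the article, and 10 is one value in a range that depends on assumed AUC, prevalence, score correlation and selection rule. It also overlooks the stated maximum of 234, where the excess is smaller. If only the AUC is reported, the excess is a few points at most.
- A reader might infer a threat to the trial's main result. The Primary outcome section names the number of consultations, and the QbTest scores appear under Other measures. The Abstract also lists diagnostic accuracy as primary, but that concerns the clinical diagnosis. The QbTest section itself says the test does not stand alone as a diagnostic tool.

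It may also be said that the supplier's figures imply a high AUC and therefore a smaller excess. That is fair arithmetic. However, those data are unpublished and no comparison group is stated for them, whereas this trial enrols only children referred for suspected ADHD. Separation may be weaker here, and the excess correspondingly larger.

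**Conclusion.** The point holds in a conditional and limited form. The article plans to obtain the most discriminating QbTest model from its own sample and describes no correction. Any performance reported for that model from the same children would be optimistic. With three scores, AUC 0.65 to 0.95, prevalence 50% to 70% and a best-Youden cut-off, the excess is about 0 to 4 points in AUC. If a cut-off is chosen, sensitivity plus specificity would be roughly 4 to 14 points too high in sum at N = 142 to 178 and 3 to 9 at N = 234, with somewhat more if score subsets are searched. The direction is certain. The size is not derivable from the article and rests on these assumptions. The primary outcome, the sample size and the between-arm accuracy comparison are untouched, so this is a modest improvement to an exploratory analysis.

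**What to change.** State that the QbTest ROC model is exploratory. Report its AUC corrected for optimism by bootstrap, and its sensitivity and specificity corrected in the same way if a cut-off is chosen. Each resample should repeat the whole procedure: selection of scores, estimation of weights and choice of cut-off. Correcting only the last step would leave part of the optimism in place. Give the corrected figures as the main result with the uncorrected ones alongside, and fix the cut-off rule and the candidate scores in advance. If a full protocol or SAP already does this, cite it.

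The cost is a little more analysis code and slightly less favourable accuracy figures. Design, data collection, sample size and the primary analysis do not change.

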**Figure 1 BMJOPEN2014006838F1:**
[figure not shown]
Study flow chart. ADHD, attention deficit/hyperactivity disorder; CAMHS, Child and Adolescent Mental Health Services.

Phase 1, Assessment: The first phase investigates the use of QbTest as a tool to aid diagnosis. Participants will undergo ADHD ‘assessment as usual’, which varies between clinics, clinicians and cases, but will typically involve an interview with the parent/young person and collection of questionnaires from the parent/young person and teacher. While attending the clinic, the participant will be asked to complete the QbTest at some point during the diagnostic process. Participants will also be asked to complete baseline outcome measures (see measures section).

Phase 2, Treatment: Patients who receive a clinic diagnosis of ADHD and are allocated by clinicians to receive ADHD medication initiated within 3 months of their baseline assessment will be asked to complete a second QbTest (Qb2) 4–8 weeks after medication initiation. This timeframe was chosen to ensure that all participants can complete their second QbTest before the 6-month follow-up.

All participants will stay in the trial for 6 months and will be asked to complete outcome measures at 3 and 6-month follow-up, regardless of their diagnosis or whether they receive medication. With the aim of promoting participant retention and completion of follow-up measures, participants will be compensated for their time with a £15 high-street voucher if they remain in the trial until 6 months.

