### Randomisation and blinding

Once consent has been obtained from participants, their information will be entered onto a web-based randomisation system (set up by University of Nottingham Clinical Trials Unit; CTU). The arm to which a participant is assigned will be determined by a computer generated pseudo-random code using random permuted blocks of varying size, created by the Nottingham CTU in accordance with their standard operating procedure and held on a secure server. Participants will be allocated with equal probability to each arm (QbO and QbB) with stratification by site. All participants will undergo the same research measures, including the QbTest. It is the time at which the report is made available to the clinician and patient that is randomised (immediately vs 6 months later). Outcome assessors for all measures will be blind to which arm the participant is in. There are no anticipated events.

In which participant unblinding would be necessary. There is an allocated unblinded research team member ([name]) to provide control checks where required.

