For time to event variables such as time to diagnosis (in days), survival analysis using log-rank test will be performed for group comparison and Kaplan-Meier survival curves will be displayed for each group. Logistic regression will be used to compare the proportion of normalisation between two groups at 6-month follow-up time. For all regression modelling to explore the difference between arms, group status will be included as explanatory variables. Data transformation would be needed for skewed outcome variables.

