## Study limitations

The diagnosis and management of ADHD is inconsistent, as such the ‘assessment as usual’ practice will vary across sites. In order to document this difference each site completed a questionnaire prior to their participation in the trial detailing their ‘assessment as usual’ procedure. Furthermore, basic descriptions of ‘assessment as usual’ will be recorded in the pro-forma (such as number and length of appointments, decision-making and medication). Given this is a pragmatic trial conducted in real-world settings we are interested in the impact of adding QbTest feedback to ‘assessment as usual’—without changing other aspects of practice. In order to minimise the trial results being influenced by practice in any one site, we are recruiting participants across multiple sites in different regions of the country and include both CAMHS and community paediatrics. In our design, we have attempted to control for variations between sites by stratification of randomisation by site.

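### Randomisation is stratified by site, but the primary Poisson model is stated with group status as its explanatory variable and no planned between-arm analysis names site

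*Protocol article*

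**What the plan says.** Protocol article, Randomisation and blinding: "Participants will be allocated with equal probability to each arm (QbO and QbB) with stratification by site". Study limitations expects usual assessment to differ from site to site and offers the stratified design as the response: "we have attempted to control for variations between sites by stratification of randomisation by site".

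Data analysis plan:
- Primary outcome (number of visits to a confirmed or excluded diagnosis): "Poisson regression with binary group status as the explanatory variable will be implemented".
- Treatment-related scores (SNAP-IV, side effects, SDQ, C-GAS): "multilevel modelling with patient as a level 2 unit will be again applied to quantify the difference between QbO and QbB arms". Clinician confidence is handled in the same way. No site level is named.
- Days to diagnosis: "survival analysis using log-rank test will be performed for group comparison". No stratification of the test is mentioned.
- Stability of diagnosis and normalisation: logistic regression, with no site term named.
- General rule: "For all regression modelling to explore the difference between arms, group status will be included as explanatory variables".

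Trial phases adds: "Participants will also be asked to complete baseline outcome measures". No model names a baseline score as a covariate.

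**The concern.** Stratifying by a prognostic factor makes the arms alike on that factor. The true sampling variation of the arm comparison then falls, but the reported standard error reflects this only if the analysis also takes account of the factor. Otherwise, in many models, between-site variation stays in the error term, the reported standard error exceeds the true one, and the test is conservative. The number of visits is a direct product of local assessment practice, so site is a plausible prognostic factor here.

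A later analysis plan could add site. For the primary outcome, though, that would change a model the article already states. What is at stake is precision and agreement between design and analysis, not bias. For scores measured at baseline, leaving the baseline value out would also waste information already collected.

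**Working it through.** **Inputs from the documents.** Mean visits 2.94 and 2.18, two-sided 0.05, 80% power, Poisson counts, 71 per group, 178 in total after 20% attrition, 234 at 90% power (Sample size and justification); nine NHS Trusts (Setting). The documents give no between-site variance and no baseline correlation, so both are assumed below over a range.

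**1. Reproducing the sample size.** n per arm = (z₀.₉₇₅ + z_power)² × (1/2.94 + 1/2.18) / [ln(2.94/2.18)]².
- 80% power: 70.09, so 71 per arm; 142/0.8 = 177.5, so 178. Both agree with the protocol.
- 90% power: 93.84, so 94 per arm; 188/0.8 = 235 (234.6 without rounding n). The protocol's 234 agrees to within rounding.

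**2. Primary model with ordinary standard errors.** With group alone, Var(log rate ratio) = 1/(visits in arm 1) + 1/(visits in arm 2). At the design values this is 1/(71 × 2.94) + 1/(71 × 2.18) = 0.01125, so SE = 0.106. Site effects balanced between arms do not enter this formula.

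**3. Simulation.** 142 analysed patients, nine near-equal sites, blocks of two within site, rate ratio 2.18/2.94, 1,500 runs per setting. Monte Carlo error on power is about √(0.8 × 0.2/1500) = 1 percentage point.

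| Assumed site SD (log scale) | Model-based SE, group only / with site | Power, group only / with site | Robust SE, group only | Power, robust, group only |
|---|---|---|---|---|
| 0 | 0.106 / 0.106 | 80.3% / 80.1% | 0.105 | 81.2% |
| 0.15 | 0.106 / 0.106 | 78.7% / 79.1% | 0.108 | 77.7% |
| 0.30 | 0.107 / 0.107 | 81.3% / 81.2% | 0.116 | 77.3% |
| 0.45 | 0.107 / 0.107 | 81.2% / 81.1% | 0.128 | 69.8% |

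The group-only estimate actually varied with SD 0.104 at site SD 0.30 and 0.108 at 0.45. The robust errors of 0.116 and 0.128 are therefore too large, and type I error fell to 4.3% and 2.5%. A rough formula agrees: at SD 0.30 the extra relative variance per arm is exp(0.09) − 1 = 0.094, so SE ≈ √[(0.799 + 2 × 0.094)/71] = 0.118.

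The comparator used here is the site-adjusted model with ordinary errors (81%). The site-adjusted model with robust errors gave 82.6% at SD 0.30, but its SE (0.103) was slightly below the empirical 0.104, so that figure flatters the adjusted analysis.

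**4. Log-rank test.** 144 patients, nine sites of 16, no censoring, assumed log hazard ratio 0.5. Power, unstratified v stratified:
- Site SD 0.3 on the log hazard: 80% v 78%.
- Site SD 0.5: 73% v 78%.
- Site SD 0.7: 65% v 78%.

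Unstratified type I error was 3.4% at SD 0.5 and 2.2% at 0.7; stratified, it was about 5%.

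**5. A continuous score at one time point,** same layout. At an assumed between-site intraclass correlation of 0.10, type I error was 4.1% without site and 4.9% with it, and power 81% v 83%. At 0.20 the figures were 3.5% v 5.2% and 82% v 88%.

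**6. Baseline adjustment of scores.** Residual variance is multiplied by 1 − r², relative to an analysis that ignores baseline: 0.91, 0.75 and 0.51 for assumed r = 0.3, 0.5 and 0.7.

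**The case against.** A reader might infer that omitting site overstates the variance of the primary analysis and costs it power. As written, it does not. The article specifies Poisson regression and mentions no robust or scaled errors; with ordinary errors, steps 2 and 3 show no loss. This objection stands in full, and the loss for the primary outcome applies only if another type of error is used.

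The only evidence on site in the document also points away from a large effect. Sample size and justification reports that visit counts in the audit were similar between centres and assumes no centre effect. At site SD 0 nothing is lost under either type of error. That stands too, although it sits beside the statement in Study limitations that practice will differ between sites.

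Three further readings go too far:
- **Group status is the only term in every model.** The general rule says that group status will be included and does not exclude other terms. The primary-model sentence is the firmer basis.
- **Hazard and odds ratios are attenuated by inflated errors.** No hazard ratio is planned. In logistic regression, adjusting for site changes the estimand from a marginal to a conditional odds ratio and usually raises its standard error.
- **Baseline is ignored.** The visit count has no baseline value. The multilevel score models may already carry baseline as a repeated outcome; the article does not say, and a condensed article may leave this to the analysis plan.

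What survives is that the stratification factor appears in no stated analysis, including the one primary model whose explanatory variable is spelt out.

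**Conclusion.** The point holds as a mismatch between design and analysis, not as a defect that biases results or inflates type I error. For the primary outcome with ordinary Poisson errors, adding site changes neither the standard error nor power to any material degree, and 71 per arm remains sufficient under the protocol's own assumptions. With robust or scaled errors, group-only power would be about 77% v 81% at an assumed site SD of 0.30 and about 70% at 0.45, with no loss at 0. The unstratified log-rank test and the score models become conservative if sites differ appreciably. The gain from baseline adjustment depends on a correlation the documents do not give. Every figure other than the reproduced sample size rests on an assumed site variance, effect size or correlation. The change is worth making because it is free and the protocol itself expects sites to differ.

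**What to change.** - Include site in the primary Poisson model and in the secondary between-arm regressions, as a fixed or random effect, with a pre-stated rule for pooling small sites.
- State the type of standard error for the Poisson model (model-based, scaled or robust).
- Stratify the log-rank test by site. This has a price if sites barely differ: about two points of power at site SD 0.3 in the check above, and more as the differences approach zero. The choice should therefore be fixed in advance.
- For the logistic models, say whether the target is the marginal or the site-conditional odds ratio.
- For scores measured at baseline (such as SNAP-IV, SDQ and C-GAS), adjust for the baseline value and estimate the arm effect at the 3- and 6-month follow-ups through a group-by-time term, so that the effect is not averaged over a time before any effect can exist.

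The cost is analysis wording only. Site is held by the randomisation system, baseline measures are already collected, and the sample size does not change.
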